#### Data Collection Schedule

The study schedule for the quantitative component (Table 2) consisted of the following steps:

An initial step for the 8 departments, comprising the inclusion visit and initial data collection at the baseline (T0) and an information meeting on MM followed by an assessment of MM representations (after the MM information meeting/before the MM test session; T1), followed by the randomization of departments;An MM practice intervention for the 4 departments in the intervention group, comprising an MM test session followed by an evaluation of MM representations (T2) and the MM program; andA follow-up step for the participants of the 8 departments, with measurements of outcomes at the end of the MM program (T3) and at 3 months after the end of the program (T4).

Sociodemographic, professional, psychological, and health data were collected at T0.

The study schedule for the qualitative component in the intervention group (Table 1) comprised the following:

FG:

Interdepartment or longitudinal 1-hour FG with department managers were conducted prior to the MM program (T2) and after the MM program (T3, within 1 month after the end of the MM program) following the individual interviews. During the MM program, an additional FG might be conducted at the request of department managers in order to address any emerging needs related to the implementation. The objectives and themes were to explore and describe the barriers and facilitators to the implementation of the intervention and the group dynamics in each department; explore the variety of contexts in each department; identify the rapid adaptations that would be necessary due to barriers that could compromise implementation; identify the evolution of group dynamics and the mechanisms promoting or compromising implementation; and identify the mechanisms and effects of the intervention and their sustainability.Four 1-hour intradepartmental FG were held at T4 with all the volunteer participants. The objectives and themes were to explore and describe the barriers and facilitators to implementation as well as the group dynamics in each department and to explore and describe in depth the mechanisms and effects produced by the intervention. This included assessments at the team level and in the care relationship with patients and/or families.

Nonparticipant observation of MM session: during the MM sessions, 1 to 3 observations were conducted per department during the first month and before the end of the MM program. The objectives and themes were to observe the material conditions of the sessions; observe the attitudes and behaviors of professionals during the sessions; observe group dynamics during the sessions with the trainer; and observe nonverbal interactions between participants and with the trainer.Individual interview: a 1-hour semistructured individual interview was proposed after T3, on a voluntary basis, to participants from each department. The objectives and themes were to explore the psychic mechanisms involved in the MM intervention and to explore the effects of the intervention on the relational, managerial, and work organization dimensions. Data saturation was expected to be reached with approximately 15 to 20 participants; the theoretical maximum sample size was 60 participants. Efforts were made to ensure sex, age, and profession balance among participants. Data collection was discontinued once data saturation was deemed sufficient (Table 1).

The topic guides are provided in Multimedia Appendix 1.

#### Study Outcome Measures

The primary outcome measure was the evolution of psychological flourishing at work (EEPMT-13) at T0 and at T3. It was measured using the adapted and validated French-language scale Psychological Flourishing at Work (EEPMT-8) [9], to which the Professional Life Satisfaction Scale (ÉSVP-5) [60] was added to form a new 13-item Psychological Flourishing at Work Scale (EEPMT-13).

The secondary outcome measures were as follows:

Evaluation of the impact of the MM program between T0, T3, and T4 at (1) the individual level and (2) the department level: at the individual level, mindfulness was measured using the Five Facets Mindfulness Questionnaire (FFMQ-15; 15 items) [61], hostility, aggression, or anger was measured by the Aggression Questionnaire (AQ-12; 12 items) [62]; impulsivity was measured using a Visual Analog Scale (VAS); perceived stress was measured using the Chamoux-Simard Scale (3 questions as a VAS) [63]; the experience of being disturbed by conflict was measured using a VAS; and patient support was measured using a VAS. At the department level (collective level), job strain was measured using the Job Content Questionnaire (26 items) [64]; collective activity was measured using Likert scales (4 items) [65-67]; organizational leeway was measured using Likert scales (4 items) [68]; and psychological safety at work was measured using a VAS.

The evolution of professionals’ representation of MM:

For all participants, it was measured between T0 and T1 using the credibility and expectancy questionnaire (adapted Devilly and Borkovec Credibility/Expectancy Questionnaire; 6 items) [69].For participants in the intervention group, the evolution of MM representation between T1, T2, T3, and T4 was measured using the credibility and expectancy questionnaire (adapted Devilly and Borkovec Credibility/Expectancy Questionnaire; 6 items) [69].

Description of professionals’ representations of MM and their evolution: the description was obtained through observation reports (during the MM program) and through verbatim responses from interdepartmental FG before the program, from semistructured interviews (T3, after quantitative evaluation), from interdepartmental FG after the MM program (T3, after quantitative evaluation), and from intradepartmental FG away from the MM program (T4, after quantitative evaluation).Description of the implementation of the MM intervention: the implementation was described in terms of fidelity (number of sessions conducted, number of participants in sessions, duration of sessions, and daily practices); barriers and facilitators to the implementation of the MM program in the context of hospital departments, identified using verbatim responses from the FG and semistructured interviews; and observation reports as well as adherence to the intervention in terms of attendance at in-person practice sessions, time spent practicing MM outside sessions, and daily life practice (3 items: number of formal and informal sessions per week and time spent at T0, T3, and T4; monitoring by e-learning support).Exploration and description of the effects of the intervention and the mechanisms by which they are produced in different departments, looking for CMOCsCompliance with the intervention: deviations from the protocol were tracked and reported in terms of adherence to the protocol (sessions taking place, schedule respected), by tracking attendance at program sessions, accessing audio support material between sessions, and the MM practice outside sessions. The MM trainer is attentive to group dynamics and provides feedback to the study team.

The English translation of the PROMIND questionnaire (original in French) is provided in Multimedia Appendix 2.

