Interdepartmental FG^i^	—	—	—	✓	—	✓	—
Nonparticipant observation of MM^j^ session	—	—	—	—	✓	—	—
Individual interviews	—	—	—	—	—	✓	—
Intradepartmental FG	—	—	—	—	—	—	✓

a Not applicable.

b T0: the baseline.

c T1: after the MM information meeting/before the MM test session.

d T2: after the MM test session.

e T3: after the end of the MM program.

f T4: 3 months after the end of the MM program.

g d: days.

h M: months.

i FG: focus group.

j MM: mindfulness meditation.

**Table 2. T2:** Schedule for quantitative evaluations in the PROMIND study.

	Study stage					
	Inclusion-baseline	—^a^	Allocation	—		End of the study
Time point	T0^b^	T1^c^	—	T2^d^	T3^e^	T4^f^
Months	M1-M6^g^	M6	—	M7 ± 15 d^h^	M12 ± 30 d	M15 ± 30 d
Enrollment	✓	—	—	—	—	—
Eligibility screen	✓	—	—	—	—	—
Informed consent	✓	—	—	—	—	—
Allocation	—	—	✓	—	—	—
Quantitative assessments						
Sociodemographic characteristics: questions	✓	—	—	—	—	—
Psychological flourishing in the workplace: EEPMT-13^i^	✓	—	—	—	✓	✓
Mindfulness: FFMQ-15^j^	✓	—	—	—	✓	✓
Hostility/aggression/anger: AQ-12^k^	✓	—	—	—	✓	✓
Impulsivity: VAS^l^	✓	—	—	—	✓	✓
Perceived stress: Chamoux-Simard Scale	✓	—	—	—	✓	✓
Patient support: VAS	✓	—	—	—	✓	✓
Credibility and expectations of MM^m^ intervention: credibility and expectations adapted	✓	✓	—	✓^n^	✓^n^	✓^n^
Occupational stress (working conditions-social support at work): Job Content Questionnaire	✓	—	—	—	✓	✓
Experience of conflict-related disturbance: VAS	✓	—	—	—	✓	✓
Evaluation of collective activity: VAS	✓	—	—	—	✓	✓
Evaluation of organizational leeway: VAS	✓	—	—	—	✓	✓
Psychological safety: VAS	✓	—	—	—	✓	✓
MM practice time (outside MM sessions): questions	✓	—	—	✓^n^	✓	✓

a Not applicable.

b T0: the baseline.

c T1: after the MM information meeting/before the MM test session.

d T2: after the MM test session.

e T3: after the end of the MM program.

f T4: 3 months after the end of the MM program.

g M: months.

h d: days.

i EEPMT-13: Echelle Epanouissement Psychologique Milieu de Travail-13.

j FFMQ-15: Five Facets Mindfulness Questionnaire-15.

k AQ-12: Aggression Questionnaire-12.

l VAS: Visual Analog Scale.

m MM: mindfulness meditation.

n Intervention group (IG) only.

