###### Analysis of Secondary Outcomes

Quantitative secondary outcomes (overall score and questionnaire dimensions) will be described for the population, by demographic variable modality and by intervention group, using standard descriptive statistics. These quantitative criteria will be compared between the 2 groups using the Student *t* test or the Wilcoxon-Mann-Whitney test, according to the distribution.

Categorical secondary outcomes will be summarized for the total population, by demographic variable modality and by intervention group, using the following descriptive statistics: frequencies and percentages for each variable level and for missing values. These categorical criteria will be compared between the groups using the Chi-square test or Fisher exact test, according to the distribution.

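### The only stated test for quantitative secondary outcomes, a two-group comparison, does not fit the MM-representation outcome, which is a within-person change with no between-arm contrast after randomisation

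*Protocol article*

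**What the plan says.** All references are to the protocol article.

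- **Study Outcome Measures** lists the evolution of professionals' representation of MM as a secondary outcome, measured with a 6-item credibility and expectancy questionnaire. It has two parts. The first: "For all participants, it was measured between T0 and T1 using the credibility and expectancy questionnaire". The second: "For participants in the intervention group, the evolution of MM representation between T1, T2, T3, and T4 was measured".
- **Table 2** (in the Overview of Evaluation and Data Collection) agrees. The questionnaire is ticked at all five time points, and T2, T3 and T4 carry the footnote "Intervention group (IG) only".
- **Data Collection Schedule** fixes the order of events. The T1 assessment is placed "after the MM information meeting/before the MM test session; T1), followed by the randomization of departments". Allocation of the Groups also puts randomisation after the information meeting, and The MM Information Meeting says that the meeting was open to all 8 departments.
- **Analysis of Secondary Outcomes** first plans descriptive statistics for the population, by demographic variable and by intervention group. Its inferential rule is then: "These quantitative criteria will be compared between the 2 groups using the Student *t* test or the Wilcoxon-Mann-Whitney test". It makes no exception for any questionnaire and names no paired or longitudinal method.
- **Analysis of the Primary Outcome** specifies a multilevel model, but only for EEPMT-13, at T0 and T3 and then at T0 and T4.

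**The concern.** The outcome asks whether people's view of MM changed: after the information meeting in everyone, then through the test session, the programme and follow-up in the intervention group. Both are within-person questions. The stated test asks a different one, namely whether the two arms differ. For this questionnaire that question has no useful answer in either interval. Before randomisation there is nothing for the arms to differ by except chance, and after randomisation only one arm is measured.

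If the rule is followed literally, the report would carry a p-value for T0-T1 that looks like a result about the information meeting but is really a check of chance imbalance between future arms. For T1 to T4 it would carry no inference at all. The pilot means to learn about mechanisms and acceptability, and this questionnaire is collected at five time points for that purpose. Analysis is reported as still in progress, so the rule can still be amended before results are written up.

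**Working it through.** The documents give no sample size, power or effect size for this outcome, so there is no stated figure to reproduce. The check is mainly a comparison of the outcome definition with the stated test, interval by interval.

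**Step 1. Which data exist**

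| Time point | Relative to randomisation | Intervention group | Control group |
|---|---|---|---|
| T0 | before | collected | collected |
| T1 | before | collected | collected |
| T2, T3, T4 | after | collected | not collected |

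**Step 2. The between-group test at T0-T1**

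All 8 departments were offered the same information meeting and none had been allocated. The expected difference between arms in the T0-T1 change is therefore 0, whether the meeting changed views a lot or not at all. A test at the two-sided 5% level (stated for the primary test; assumed here) rejects with probability 5.0%, computed for 54 and for 60 people per arm.

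A simulation with 60 per arm, a common T0-T1 shift of 0.3 SD and independent observations gave rejection rates of 5.2%, 4.4%, 5.0% and 4.8% when the later programme effect was 0, 0.3, 0.5 and 0.8 SD. The test responded neither to the shift at the meeting nor to the later effect. Clustering by department would change the false-positive rate of a plain t test, but not the fact that the null is true.

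**Step 3. The between-group test at T2, T3 and T4**

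The control sample size is 0 by design, so a two-sample test is undefined.

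**Step 4. What can be estimated**

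- The T0-T1 change, both arms pooled, in everyone with both measures (8 departments).
- The changes across T1, T2, T3 and T4 in the intervention group (4 departments).

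**Step 5. Illustrative precision for T0-T1**

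Inputs: n is at most 108, the number enrolled according to Results. The number with both T0 and T1 is not given and may be lower. The T0-T1 correlation r is not given, so a range is assumed. In units of the SD at one time point, ignoring department, SE = sqrt(2(1 - r)/n):

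- r = 0.4: sqrt(1.2/108) = 0.105
- r = 0.6: sqrt(0.8/108) = 0.086
- r = 0.8: sqrt(0.4/108) = 0.061

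Clustering of changes within departments makes this larger. Take r = 0.6 and 108/8 = 13.5 people per department. An assumed intraclass correlation of the change of 0.05 gives a design effect of 1 + 12.5 × 0.05 = 1.625 and an SE of sqrt(0.8 × 1.625/108) = 0.110. An assumed between-department variance of the change of 0.07, which is an intraclass correlation of 0.07/0.87 = 0.08, gives sqrt(0.8/108 + 0.07/8) = 0.127.

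**The case against.** The best reply is that the secondary-outcome section states a general rule and never names this questionnaire. Study Outcome Measures separates the impact of the programme, measured in both arms at T0, T3 and T4, from the evolution of representations, defined as before-after. A sensible analyst would apply the two-group test to the first kind only, and could not apply it to T2-T4 by mistake because it cannot be run. A within-person test may be named in a fuller plan that is not shown, and a condensed article need not repeat it. The study also disclaims confirmatory scope.

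Part of this stands. Silence about a paired test would not by itself be a fault in an article. Here, however, the article does state a rule for the whole class of outcomes, without exception, and that rule does not fit an outcome the same article defines. For T0-T1 the misfit is not self-correcting, because the test can be run and will return a p-value.

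Three stronger readings might be inferred, and the document supports none of them:

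- *That the data would go unused.* Description for the population would show T0 and T1 levels, and description by group would show the intervention-group series. A qualitative description of representations and their evolution is also planned, with later integration. What is lacking is an estimate of within-person change with its uncertainty.
- *That one-arm collection at T2-T4 is a design error.* For an outcome defined as before-after in that arm it is coherent. Only the pairing with a two-group test fails.
- *That there are about 108 T0-T1 pairs.* That figure is enrolment, and no T1 completion figure is given.

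**Conclusion.** The concern holds as a mismatch between one secondary outcome and the only inferential method stated for its class. At T0-T1 the two-group comparison has a true null and says nothing about the information meeting. At T2-T4 it cannot be computed. Description of levels remains, but no stated analysis targets the change that defines the outcome.

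These conclusions rest on the document's own timing and collection schedule and need no numerical assumption. The precision figures do: about 0.06 to 0.11 SD for T0-T1 before clustering, from at most 108 pairs and r between 0.4 and 0.8. They show only what a suitable analysis could deliver, not the size of any harm.

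The reach is limited to one secondary outcome in an exploratory pilot. The EEPMT-13 analysis does not depend on it. It is worth correcting because the correction is cheap and the data are already in hand.

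**What to change.** State in Analysis of Secondary Outcomes that the between-group tests do not apply to the credibility and expectancy questionnaire. In their place:

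- Estimate the T0-T1 change in all participants with both measures.
- Estimate the changes across T1, T2, T3 and T4 in the intervention group.
- For both, use a paired or repeated-measures model with time as a fixed factor and a participant random effect. Allow for department in a simple form and use small-sample degrees of freedom: there are 8 departments for T0-T1 and only 4 for T1-T4. A richer structure, such as department-by-time random effects, would be fragile with four departments.
- Report mean changes with 95% CI, labelled as uncontrolled, exploratory before-after changes, alongside the planned descriptive statistics and with the number of pairs behind each estimate.

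The cost is a change of wording and one extra model, with no new data. The drawback is that the T1-T4 intervals will be imprecise, and the report should say so.

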### Data Analysis

#### Quantitative Analysis

##### Number of Subjects

As this is a pilot study, the number of participating departments (N=8) and the number of professionals studied (15 professionals per department; N=120) were not determined by a power calculation [70] but by the operational constraints of the study, notably the maximum number of subjects recommended by the MM trainer for a group of meditative practice [55,71,72].

##### Statistical Methods

The primary objective of this study is to compare the evolution (between T0 and T3) in psychological flourishing at work in the intervention group compared with the control group.

###### Analysis of the Primary Outcome

For each individual, the psychological flourishing at work was measured (using EEPMT-13) at 2 time points: T0 and T3. Since each individual has 2 measures, and each individual belongs to a given department, we will use a multilevel model for the analysis of the primary outcome [73]. These models, also known as mixed models, are particularly well-suited to the analysis of this type of hierarchical data (ie, first level=the measure, second level=the individual, and third level=the department).

Noting Y_ijk_ as the EEPMT-13 measure j of individual i in department k, we obtain the following model 1 equation:

$$Y_{ijk}=\beta_{0}Z_{k}+u_{ik}+v_{k}+\beta_{1}{\;}^{*}X_{ijk}+\beta_{2}X_{ijk}G_{k}+e_{ijk}$$

where u_ik_, v_k_, and e_ijk_ are, respectively, the individual random effect (individuals having greater or lesser flourishing), the department random effect (certain departments presenting on average greater or lesser levels of flourishing), and the residual deviation of the ijk measure; Z_k_ is a vector of binary indicator variables indicating the department type of department k; G_k_ is an indicator variable for the intervention group (0 if the department belongs to the control group and 1 if the department has received the intervention); X_ijk_ is a measurement time indicator variable (0 if the measurement is taken at T0 and 1 if it is carried out at T3).

With this coding, the 4 fixed parameters making up the β_0_ vector provide mean levels according to the department type (which is a stratification factor in randomization), the parameter β_1_ corresponds to the variation between T0 and T3 for departments belonging to the control group, and β_1_ + β_2_ corresponds to the variation between T0 and T3 for departments belonging to the intervention group. The parameter β_2_ thus corresponds to the parameter of interest that describes the effect of the intervention, and the main hypotheses tested will be as follows:

H0: evolution between T0 and T3 is identical between the 2 groups (ie, β_2_=0)

H1: evolution between T0 and T3 is not identical between the 2 groups (ie, β_2_≠0)

This test will be performed using the Wald test (2-tailed test, type I error rate=5%).

It will be investigated whether a residual effect of the intervention persists at T4, by analyzing the 2 measurements at T0 and T4 in a model similar to model 1.

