### Allocation of the Groups

Randomization was carried out by the biostatistics team after the MM information meeting. Randomization was carried out at the department level and stratified by department type (medicine, geriatrics, anesthesia-intensive care, and intensive care/neonatology) to ensure that each department type was represented in both the intervention group (4 departments) and control group (4 departments). Cluster randomization was chosen to prevent contamination within departments, as professionals work closely together.

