## Results

The PROMIND study was funded in October 2021, and the funding was extended in June 2024. This study was conducted from May 2024 to June 2025. In total, 108 participants were enrolled in the study; data collection ended on June 30, 2025. Data analysis is in progress. After data analysis, the COPR will be asked to discuss the results and prospects for implementing MM based on the study findings. Workers’ representatives will be informed of the results. A dedicated meeting to summarize and discuss the results of PROMIND will be planned with the participants.

We expect the results of this study to be published by the end of 2026. Scientific publications and communications (national and international) will be planned to publicize this trial and its findings in the fields of psychiatry, public health, and occupational health. Recommendations for publication in the field of epidemiology and realist evaluation will be followed.

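### The 5% level of the Wald test of β2 is not assured with 4 + 4 randomised departments, mainly because model 1 has no department-by-time random effect

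*Protocol article*

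**What the plan says.** Under Allocation of the Groups, the Protocol article makes the department the unit of randomisation: "Randomization was carried out at the department level and stratified by department type". There are four department types, and "each department type was represented in both the intervention group (4 departments) and control group (4 departments". That is one department per arm in each of four strata, 8 in all.

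Under Number of Subjects, 15 professionals per department (120 in total) were planned on operational grounds. Under Results: "In total, 108 participants were enrolled in the study; data collection ended on June 30, 2025".

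Under Analysis of the Primary Outcome, model 1 has a random intercept for the individual, a random intercept for the department, and a residual: "the department random effect (certain departments presenting on average greater or lesser levels of flourishing), and the residual deviation of the ijk measure". Department type enters as a fixed effect on the mean level. Time and time-by-group are fixed, and there is no term that lets departments differ in their change over time. The coefficient β2 "corresponds to the parameter of interest that describes the effect of the intervention, and the main hypotheses tested will be as follows". The test is then fixed: "This test will be performed using the Wald test (2-tailed test, type I error rate=5" (5%). A T0 to T4 analysis is to use a similar model. No small-sample method is named.

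**The concern.** The intervention is assigned to departments, so chance differences between departments in their T0 to T3 change are part of the error against which β2 must be judged. Staffing, a change of head nurse or a winter surge can shift a whole department between the two measurements. Model 1 allows departments to differ in level but not in change. Any such shift is therefore treated as if it came from independent individuals, and the standard error of β2 is too small.

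A second, smaller problem sits on top. Even with the right standard error, department-level variation is estimated from 8 units, and a normal cut-off of 1.96 ignores that.

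The document states hypotheses and a 5% error rate, and it intends the results to inform larger-scale implementation. If the real error rate is two to four times the stated one, a chance difference between departments can be read as an effect on flourishing.

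**Working it through.** **Inputs from the document.** Two-sided 5% Wald test; 8 departments, 4 + 4; 15 planned per department; 108 enrolled, so 108/8 = 13.5 per department; model 1 without a department-by-time effect.

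**Assumptions not in the document.** Total variance 1; residual share σe² = 0.4; ICC ρ (department share of variance at one time point) 0.01-0.10; cluster autocorrelation CAC (correlation of a department's effect between T0 and T3) 0.5-1.0, where 1.0 means that departments do not differ in their change.

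**1. The stated figure.** 2·P(Z > 1.960) = 5.0%. This holds only if the statistic is standard normal and its standard error is right.

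**2. The missing term.** The true variance of a department's mean change is 2ρ(1 − CAC) + 2σe²/n. Model 1 allows for about 2σe²/n. The ratio is

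DE = 1 + nρ(1 − CAC)/σe², with approximate true size 2·Φ(−1.96/√DE).

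- n = 15, ρ = 0.05, CAC = 0.8: DE = 1 + 15 × 0.05 × 0.2/0.4 = 1.375, size 9.5%.
- n = 15, ρ = 0.10, CAC = 0.5: DE = 1 + 15 × 0.10 × 0.5/0.4 = 2.875, size 24.8%. This is slightly high, because the fitted residual variance absorbs some of the department variation.

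**3. Model 1 fitted by REML under H0** (6,000 runs each, 1.96 cut-off):

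- CAC = 1.0, 15 per department: 5.5% (ICC 0.01), 6.3% (ICC 0.05), 6.1% (ICC 0.10). With 13 per department and ICC 0.05: 5.6%.
- ICC 0.05, CAC 0.8: 9.6% (15 per department), 9.3% (13 per department).
- ICC 0.05, CAC 0.5: 14.5%. ICC 0.10, CAC 0.5: 23.5% (both 15 per department).

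**4. Comparison of remedies.** Change-score simulation under H0, 13 per department, 200,000 runs, σe² = 0.4:

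| ICC, CAC | Model 1, 1.96 | + department-by-time, 1.96 | + department-by-time, t with 6 df | t test on 8 mean changes |
|---|---|---|---|---|
| 0.05, 1.0 | 5.2% | 4.1% | 1.2% | 5.0% |
| 0.02, 0.8 | 6.7% | 4.8% | 1.6% | 5.0% |
| 0.02, 0.5 | 8.8% | 5.8% | 2.1% | 5.0% |
| 0.05, 0.8 | 8.9% | 5.8% | 2.1% | 5.0% |
| 0.10, 0.8 | 12.4% | 7.1% | 2.8% | 5.0% |
| 0.05, 0.5 | 13.7% | 7.4% | 3.0% | 4.9% |
| 0.10, 0.5 | 20.9% | 8.8% | 4.1% | 5.1% |

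**5. The limit.** When department-level error dominates, the statistic follows t with 8 − 2 = 6 df. Then 2·P(t6 > 1.96) = 9.8%. The correct cut-off is 2.447, and 2.447/1.960 = 1.25, so the interval is 25% wider.

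**6. Correcting only the cut-off.** Model 1 with 2.447 in place of 1.96 has a size from about 2% (CAC = 1.0) to about 12% (ICC 0.10, CAC 0.5). It is too strict when model 1 holds and too lenient when departments differ most.

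**The case against.** **The estimate is mainly within-person.** In model 1, β2 rests largely on changes in about 108 individuals, so few clusters alone do little harm: 5-6% when the model is true. This stands. The few departments matter seriously only if departments differ in their change, and the document gives no data on that.

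**The normal reference is not spelled out.** The article gives neither 1.96 nor degrees of freedom, and a fuller analysis plan might refer the Wald statistic to a t distribution. That is fair, but it would not rescue model 1. Its degrees of freedom for β2 would come mainly from individuals, so the cut-off would barely move and the standard error would be unchanged.

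**The study is exploratory.** Evaluation and Data Collection disclaims confirmatory scope, Limitations links the small number of departments to caution, and Integration of Findings weighs feasibility and barriers alongside outcomes. No p-value triggers scale-up by itself. This lowers the severity. It does not make a stated 5% test a 5% test.

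**Stronger readings that a reader might infer.** None of these is supported.

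- That the true error rate is 9.8%. This is the limit for a statistic with a correct department-level standard error judged at 1.96, not the error rate of model 1.
- That it is 14.5%, from 2·P(t3 > 1.96) if the four strata are analysed as pairs. No paired analysis is planned; department type enters model 1 only as a level.
- That a stated 95% interval is wrong. The document states none; poor coverage would be a consequence of the same standard error.
- That significance is unattainable because 2^4 = 16 allocations give a smallest two-sided randomisation p-value of 2/16 = 0.125. The arithmetic is right, but no randomisation test is planned.

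**Conclusion.** The point holds in a conditional form. The plan fixes a 5% two-sided test that is not assured to have that level. The size is about 5-6% if departments share a common T0 to T3 change within each arm. It is roughly 7-23% if they do not, for ICC 0.02-0.10, CAC 0.5-0.8, residual share 0.4 and 13 to 15 people per department. Those variance assumptions are the reviewer's, so the range shows how sensitive the test is and does not estimate the error rate in this trial.

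Most of the inflation comes from the missing department-by-time effect. The reference distribution is a second, smaller contributor, worth about 5-9% at the 1.96 cut-off once the effect is added. Severity: should be fixed, not critical, because the study is an exploratory pilot.

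**What to change.** Base the test of β2 on department-level variation, in one of two ways:

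1. Compute the mean T0 to T3 change in each of the 8 departments and compare the arms by a t test with 6 df. It held about 5% in every scenario above and is the simplest choice.
2. Add a department-by-time random effect to model 1 and refer β2 to a t distribution with department-based degrees of freedom (8 − 2 = 6). This keeps the mixed model but is somewhat conservative, at 1.2-4.1% above.

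A degrees-of-freedom correction to model 1 alone is not enough. Report β2 as an estimate with a confidence interval from the same reference, and apply the same change to the T0 to T4 model.

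The article says that data analysis is in progress, so the change should be recorded and dated before the group comparison is seen. The work is one standard analysis in R. The price is a wider interval (25% wider from the cut-off alone, more where the standard error was understated) and less chance of a significant result.
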